## 2.1 Research questions and hypotheses

1. Can intake of high fat loads with different fatty acids (SFA, MUFA, PUFA) result in differential changes in **PBMC gene expression** in the different groups of subjects?

 *The PBMC gene expression profiles of the high risk subjects will be more affected compared to gene expression profiles of the healthy subjects.*

2. Can the **PBMC inflammatory response capacity** be influenced by fatty acid intake and will these changes be different for the high risk subjects?

* Obese and type 2 diabetic subjects will have an impaired inflammatory response capacity. The different fatty acids will differently influence this inflammatory response capacity*

3. Can intake of high fat loads with different fatty acids result in differential changes in **endothelial function** and will these changes be different for the high risk subjects?

 *The different fatty acid compositions of the shakes will result in different changes in endothelial function. The high fat load will result in a higher degree of endothelial dysfunction in the high-risk subjects compared to the healthy subjects.*

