### 6.3.4 Intervention

Figure 1 shows the study design and table 3 summarizes the assessments performed during the intervention.

Before the start of each study day, the Hb value of each participant will be determined by using a hemoglobin analyzer (HemoCue 201). Participants with a Hb value below 8.4 mmol/L will not be measured and are asked to make a new appointment. If Hb values are normal (e.g. above 8.4mmol/L) the measurements can be started. At T=-20 min, macro vascular regional arterial stiffness will be assessed and blood samples (62 ml) will be drawn by normal venopuncture. At T=0, the high-fat milkshake will be consumed within 15 min. Blood will be drawn 2 hours and 4 hours after intake of the shake and macro vascular regional stiffness will be assessed at the same time points.

The participants will spend the entire study duration (4.5 hours) in a room close to the blood collection room, where they will be able to read books, watch television, video or DVDs, or relax in comfortable chairs. At the end of the study day a lunch will be offered to the participants. At the end of the three study days the diaries will be collected*.*

SFA

SFA

SFA

MUFA

MUFA

MUFA

PUFA

PUFA

PUFA

SFA

SFA

SFA

MUFA

MUFA

MUFA

PUFA

PUFA

PUFA

SFA

SFA

SFA

MUFA

MUFA

MUFA

PUFA

PUFA

PUFA

Obese, diabetic subjects

Obese, healthy subjects

Lean, healthy subjects

Study day 1

Study day 2

Study day 3

Washout >1 wk

Washout >1 wk

Study day 1

Study day 2

Study day 3

T=0,2,4 hrs:

- Blood sampling

- Endothelial function measurement

T=0,2,4 hrs:

- Blood sampling

- Endothelial function measurement

T=0,2,4 hrs:

- Blood sampling

- Endothelial function measurement

Figure 1: Design of the study

Table 3: Protocol on each study day.

| **Intervention time, after 10h overnight fast** | **-20 min**  (7.00am) | **0 hr**  (7.20am) | **2 hr**  (9.20 am) | **4 hr**  (11.20 am) |
| --- | --- | --- | --- | --- |
| Consumption of high fat shake |  | x |  |  |
| Blood sampling (ml) | x |  | x | x |
| for plasma/serum isolation | 20 ml |  | 20 ml | 20 ml |
| for PBMC isolation | 42 ml |  | 42 ml | 32 ml |
| PBMC gene expression | x |  | x | x |
| PBMC stimulation with LPS | x |  | x |  |
| Cytokine profile | x |  | x | x |
| Plasma fatty acid profile | x |  | x | x |
| Plasma insulin and glucose | x |  | x | x |
| Endothelial function | x |  | x | x |
| Leukocyte activation markers | x |  | x | x |

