# STATISTICAL ANALYSIS

In this cross-over study, each subject will consume the three shakes and can be used as its own reference.

Analysis of PBMC whole genome expression data will be performed using a Bayesian linear regression model (implemented in the software package LIMMA; [www.bioconductor.org](http://www.bioconductor.org/)). Raw microarray data will be normalized using RMA quantile normalization. Statistically significant changed genes will be identified by student paired t-test followed by a false discovery rate correction (FDR) The latter is used to correct for multiple testing.

Analysis of secondary and tertiary outcome variables (endothelial function, glucose etc.) will be in SPSS version 15.0. Effects of treatment (SFA, MUFA, PUFA) within each risk group (lean healthy, obese, type 2 diabetic) will be tested by repeated measures ANOVA (mixed model) using pre-defined contrasts, i.e. 2 versus 0 hrs and 4 versus 2 hrs. Additionally, incremental areas under the curve will be calculated for all significant altered outcome variables using the trapezoïdal rule and compared between treatments using one-way ANOVA.

Differences between risk groups for each treatment will be tested by one-way ANOVA followed by LSD correction. Additionally, incremental areas under the curve will be calculated for all significant altered outcome variables and compared between risk groups using one-way ANOVA.

An empty ANOVA table providing more information about the analysis is included below.

| Variable | df |
| --- | --- |
| Risk profile (diabetic, obese, control) | 2 |
| Treatment (SFA, MUFA, PUFA) | 2 |
| Time (0,2,4) | 2 |
| Interaction | 8 |
| Error | 579 |

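### The pre-defined contrasts for secondary and tertiary outcomes omit the 4-hour change from fasting and any shake-by-time comparison, and the incremental AUC depends on an unnamed significance test

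*Protocol*

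**What the plan says.** Section 8 of the protocol (Statistical Analysis) states that "Effects of treatment (SFA, MUFA, PUFA) within each risk group" will be tested by repeated measures ANOVA (mixed model), "using pre-defined contrasts, i.e. 2 versus 0 hrs and 4 versus 2 hrs". It then adds that "incremental areas under the curve will be calculated for all significant altered outcome variables" and "compared between treatments using one-way ANOVA". The test that makes an outcome count as significantly altered is not identified.

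The ANOVA table in the same section lists risk profile (2 df), "Treatment (SFA, MUFA, PUFA) | 2", time (2 df), "Interaction | 8" and error (579 df).

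Section 2.1 sets the question. For endothelial function the hypothesis reads "The different fatty acid compositions of the shakes will result in different changes in endothelial function".

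Table 3 in section 6.3.4 schedules most measurements at -20 min, 2 h and 4 h. Ex vivo LPS stimulation is marked before the shake and at 2 h only.

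All of this concerns secondary and tertiary outcomes. PBMC gene expression, the primary outcome, has its own analysis (LIMMA, paired t-tests, false discovery rate).

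**The concern.** The sentence announces a test of the shakes and then specifies differences between times. A test of whether shakes produce different changes needs a contrast of the form (change from T=0 on shake A) minus (change from T=0 on shake B). No such contrast is named.

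The two listed steps also leave out 4 v 0 h, the total change from fasting. If a response builds slowly, each step carries only part of it and both can fall short while the total is clear.

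The iAUC could have recovered such a response, because it combines the whole curve and is compared between shakes. But it is calculated only after an outcome has passed a significance test. An outcome that fails loses that comparison, and which outcomes fail depends on an unstated choice of test.

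At stake is whether the plan answers its own questions on endothelial function, inflammatory response and plasma measures.

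**Working it through.** **1. The ANOVA table.** Observations: 3 groups x 22 men x 3 shakes x 3 times = 66 x 9 = 594. Listed model df: 2 + 2 + 2 + 8 = 14. Error df: 594 - 1 - 14 = 579, exactly the printed figure. The table is therefore complete as it stands, and no further term is hidden in it.

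**2. What the interaction row can hold.** With three factors of 2 df each, every two-way interaction has 2 x 2 = 4 df and the three-way has 2 x 2 x 2 = 8 df. Fitting them all would use 4 + 4 + 4 + 8 = 20 df and leave 594 - 1 - 6 - 20 = 567 for error, not 579. The single 8-df row equals the three-way term. No separate 4-df shake-by-time row is listed.

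**3. What the treatment row measures.** It averages each shake over all three times, including the sample taken before the shake. Suppose two shakes differ by D at 4 h, by D/2 at 2 h and not at all at T=0. The treatment row then sees (0 + D/2 + D)/3 = D/2, half the 4-hour difference. It does not measure change from fasting.

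**4. Contrast algebra.** (4 v 0) = (2 v 0) + (4 v 2). The two listed contrasts span the full 2-df time effect, so the model loses no information. What is missing is the direct test of their sum.

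**5. Size for a gradual rise.** The protocol gives no effect size, SD, correlation or alpha for these outcomes, so these inputs are assumptions: two-sided 0.05, equal variances, equal correlation r between times, and a rise of 0.35 SD by 2 h and 0.7 SD by 4 h on one shake in one risk group. The n = 20 per group comes from section 4.5.

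- SD of a paired change = SD x sqrt(2(1 - r)). At r = 0.5 this is 1.0 SD.
- Each step: d = 0.35, noncentrality 0.35 x sqrt(20) = 1.57, 19 df, power 0.32.
- 4 v 0 h: d = 0.70, noncentrality 0.70 x sqrt(20) = 3.13, power 0.84.
- At least one step significant: independence would give 1 - (1 - 0.32)^2 = 0.54. The steps share the 2 h value and are negatively correlated, so the simulated figure is higher, about 0.59.
- The 2-df test for time has simulated power 0.77.

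| Even rise to | r | Either listed step | 4 v 0 h |
| --- | --- | --- | --- |
| 0.5 SD | 0.5 | 0.36 | 0.57 |
| 0.7 SD | 0.3 | 0.46 | 0.71 |
| 0.7 SD | 0.5 | 0.59 | 0.84 |
| 0.7 SD | 0.7 | 0.80 | 0.97 |
| 0.9 SD | 0.5 | 0.80 | 0.97 |

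**6. Other shapes (0.7 SD, r = 0.5).** If the response is reached by 2 h and held, 2 v 0 h and 4 v 0 h each have power 0.84. If it appears only after 2 h, 4 v 2 h has about the same power as 4 v 0 h (0.85 for each). Only the gradual rise is exposed.

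**7. LPS stimulation.** With samples before the shake and at 2 h, 4 v 2 h cannot be formed. Only 2 v 0 h applies.

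**The case against.** Adjacent contrasts are a legitimate choice. They span the time effect, and 4 v 2 h separates continued rise from clearance. Section 1.1 cites delayed clearance in obese and diabetic subjects, so a significant return towards fasting is an informative result. This stands, and it is why 4 v 2 h should be kept.

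Contrast detail is often left to a statistical analysis plan. That carries less weight here, because the protocol itself fixes the contrasts as pre-defined and lists them.

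A reader might infer more than the documents support:

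- *That shakes are never compared.* The model is said to test treatment, the table has a treatment row, and iAUC is compared between shakes. The contrasts could even be meant as shake-by-time contrasts. The text does not say so, and the listed terms do not supply them.
- *That the two contrasts decide which outcomes get an iAUC.* The qualifying test is not named. If it is the 2-df test for time, power in the main example is 0.77 rather than 0.59.
- *That sustained responses are missed.* A response present at 2 h and held is caught by 2 v 0 h.
- *That the loss is as large as 56% against 99%.* Those are the powers of one step and of 4 v 0 h when each step is 0.5 SD of the paired change. An outcome is missed only if both steps fail, and the chance that at least one succeeds is about 88%. At 0.4 SD per step, one step has 40%, either step about 70% and 4 v 0 h 92%.
- *That significance on one shake but not another will be read as a shake effect.* Nothing in the protocol proposes that inference.

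The either-step figure also uses two uncorrected tests. With no effect, at least one is significant about 9% of the time, so it is not compared with 4 v 0 h at equal alpha.

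**Conclusion.** The point holds for secondary and tertiary outcomes. The contrasts as listed do not match the stated question: they omit 4 v 0 h, they name no shake-by-time comparison, and the ANOVA table has no separate term for one. The iAUC comparison that might compensate is conditional on an unspecified test.

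For an even rise to 0.7 SD, the chance of detection by at least one listed contrast is about 0.59, against 0.84 for 4 v 0 h. Over correlations of 0.3 to 0.7 it is 0.46 to 0.80 against 0.71 to 0.97. These figures rest on assumed effect sizes, correlations and alpha, and on the response shape least favourable to adjacent steps. They describe detection of a change over time on one shake. They do not measure power for a difference between shakes, which the protocol gives no figures to calculate.

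The primary gene expression analysis is unaffected. The change should be made but does not threaten the trial.

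**What to change.** In section 8:

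1. Keep 2 v 0 h and 4 v 2 h, and add 4 v 0 h.
2. State that changes from T=0 (2 v 0 h and 4 v 0 h) are tested as shake-by-time contrasts, that is, as differences between shakes in change from fasting, within each risk group. Include the shake-by-time term in the model and list it in the ANOVA table.
3. For LPS stimulation, specify 2 v 0 h only, in line with Table 3.
4. Calculate and compare iAUC for every outcome measured at all three times, regardless of significance.

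No new data are needed. The cost is a reworded paragraph, a revised table, slightly more output and one extra contrast per outcome, which adds somewhat to the multiplicity already present.

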### 6.1.2 Measurements of secondary study outcomes

PBMC immune response capacity

Cytokine profiles will be measured in plasma at all time points (T=0, 2 and 4 hrs) by quantitative immunoassays at Rules Based Medicine laboratories (Austin, Texas, USA). The cytokine profile of a panel of 120 proteins including adiponectin, CRP, and interleukins will be determined. For details on these 120 proteins, see: <http://www.rulesbasedmedicine.com/products-services/humanMAP-antigen.asp>

Plasma levels of additional potential biomarkers for metabolic syndrome (i.e. MBL2, FAM3D) will be measured in plasma by ELISA.

PBMC immune response will be determined by stimulation of the isolated cells ex vivo with lipopolysaccharide (LPS) for 4 hours. TNFα secreted in culture medium of the PBMC will be measured by ELISA. PBMC expression of genes involved in the acute immune response will be measured by qPCR.

Leukocyte activation markers will be determined at all time points (T=0, T=2, T=4 hrs) by using flow cytometry analysis (coulter Epics XL.MCL flow cytometry by Beckman Coulter).

Endothelial dysfunction

Macro vascular regional arterial stiffness will be assessed by Pulse Wave Analysis (PWA) (13). This is a non-invasive measurement which will be performed at every time point (T=0, 2 and 4 hrs).

A pressure sensor (applanation tonometer) is applied on the radial artery to record pressure pulse waveforms. The waveform is calibrated using systolic and diastolic pressure values from a conventional cuff measurement. From these peripheral waveforms we can derive a aortic pressure waveform and conduct a pulse wave analysis (PWA). A number of features can be extracted from a PWA, which cannot be made from the conventional measurement of brachial blood pressure. These features include the Augmentation Index (Aix) and the Subendocardial Viability Ratio (SEVR).

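### False discovery rate control stops at the genes: the 120-protein panel is tested with no adjustment across proteins, shakes or time contrasts

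*Protocol*

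**What the plan says.** Section 8 sets two standards.

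- **Gene expression.** Changed genes are identified by "student paired t-test followed by a false discovery rate correction (FDR"), and the reason is given: "The latter is used to correct for multiple testing".
- **Secondary and tertiary outcomes.** The within-group stage covers "Effects of treatment (SFA, MUFA, PUFA) within each risk group (lean healthy, obese, type 2 diabetic"), by repeated measures ANOVA "using pre-defined contrasts, i.e. 2 versus 0 hrs and 4 versus 2 hrs". The between-group stage reads: "Differences between risk groups for each treatment will be tested by one-way ANOVA followed by LSD correction". After each stage, "incremental areas under the curve will be calculated for all significant altered outcome variables" and compared by one-way ANOVA.

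Section 6.1.2 lists the plasma panel among the secondary outcomes: "The cytokine profile of a panel of 120 proteins including adiponectin, CRP, and interleukins will be determined". On timing it adds: "Cytokine profiles will be measured in plasma at all time points (T=0, 2 and 4 hrs"). Section 8 does not name the panel, but as a secondary outcome it falls under the second standard. The protocol gives no significance level for these outcomes, no order of testing and no key secondary outcome.

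**The concern.** The panel is the protocol's other high-dimensional outcome. The protocol recognises the multiplicity problem for the genes, and then prescribes for 120 proteins a method meant for one outcome at a time. The only correction named for these outcomes is LSD. It concerns the pairwise differences among three risk groups for a single outcome under a single shake, and has no bearing on the number of proteins, shakes or time contrasts.

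At stake is how far a list of changed proteins can be believed. The panel is one of the measurements listed under immune response capacity, which is a secondary objective. With no key outcome named and no adjustment across the panel, any nominally significant protein could be reported as a finding. Significance also decides which variables go on to the incremental area analysis. That analysis uses the same men and samples, so it cannot serve as independent confirmation of a protein that was selected by chance.

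**Working it through.** **Inputs.** 120 proteins (section 6.1.2); 3 risk groups, 3 shakes and 2 time contrasts (section 8); 22 men per group, 66 in all (section 3.1). Alpha is not stated. I assume 0.05 two-sided and show 0.01 and 0.10 as a range.

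**Check of the layout against the plan's own figure.** The empty ANOVA table in section 8 gives 579 error degrees of freedom. With 66 men × 3 shakes × 3 times = 594 observations, 594 − 1 − (2 + 2 + 2 + 8) = 579. The layout of 3 groups, 3 shakes and 3 times is therefore the intended one. The protocol states no false-positive count to reproduce.

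**Expected false positives.** If every null hypothesis is true, the expected number is (number of tests) × alpha. This does not require the tests to be independent.

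| Reading of section 8 | Tests on the panel | Expected at 0.05 |
|---|---|---|
| Within group: one treatment test per group | 120 × 3 = 360 | 18 |
| Within group: one treatment test per group and contrast | 120 × 3 × 2 = 720 | 36 |
| Within group: both contrasts in each of the nine group-by-shake cells | 120 × 3 × 3 × 2 = 2,160 | 108 |
| Between groups: one F test per shake | 120 × 3 = 360 | 18 |
| Between groups: one F test per shake and change | 120 × 3 × 2 = 720 | 36 |
| Between groups: one F test per shake and time point | 120 × 3 × 3 = 1,080 | 54 |
| Both contrasts in nine cells, plus one F test per shake and change | 2,160 + 720 = 2,880 | 144 |

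The 108 comes from the within-group contrasts, not from the between-group sentence that names LSD. For those 2,160 tests the figure is 21.6 at alpha 0.01 and 216 at alpha 0.10. The span of 18 to 144 covers plausible readings and is not a strict bound: pairing the 2,160 contrasts with F tests at all three time points gives 3,240 tests and 162.

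**Chance of at least one.** With a single F test on each of 120 proteins, taken as independent, it is 1 − 0.95^120 = 0.998.

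**What LSD does.** In a simulation of 200,000 trials with no true difference (three groups of 22, one outcome), the chance of at least one false pairwise difference was:

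- 0.049 when the pairs are compared only after a significant F;
- 0.120 when they are always compared.

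Both figures are for one protein and one shake. Neither version adjusts across the panel.

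**The case against.** Five points can be made on the other side.

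1. **A reader might infer that about 100 false positives are built into the plan.** The documents do not support that. The 108 needs an alpha that the protocol does not state, true nulls throughout, and one of several readings of the treatment test. The introduction and hypotheses expect real postprandial changes, and each real change removes a true null. This objection stands, and the figure can be given only as a conditional range.

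2. **A reader might infer that LSD does nothing.** That is also too strong. With exactly three groups, LSD after a significant F holds the error near 5% for one protein and one shake, and the protocol does place LSD after the ANOVA. Nor does it claim that LSD covers the whole panel. What remains is that the F condition is not stated and that LSD does not reach across proteins.

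3. **A reader might infer that research question 2 would be answered from a list dominated by chance.** Nothing supports the word dominated, because the number of true changes is unknown. Question 2 also rests on LPS-stimulated TNFα, qPCR of acute immune genes and leukocyte activation markers. This objection stands.

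4. **Multiplicity rules for secondary outcomes are often left to a SAP.** That would excuse silence. Here the protocol states the method and names the correction, so a stated choice is open to comment. This objection does not remove the point.

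5. **These are secondary outcomes, and the primary outcome already has false discovery rate control.** True, and it limits the severity.

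**Conclusion.** The point holds in a limited form. As written, section 8 gives no control across the 120 proteins, the three shakes or the two time contrasts, although it gives such control for the genes. Assuming alpha 0.05 and all nulls true, about 18 to 144 false positives are expected on the panel depending on how the tests are read, with 108 under the nine-cell reading. The number falls as real changes increase. LSD is adequate for the three group comparisons of one protein and one shake if a significant F is required, and not otherwise; the protocol leaves this open. The flaw should be corrected before the panel is analysed, but it does not touch the primary outcome.

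**What to change.** In section 8:

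- State the significance level for secondary and tertiary outcomes.
- State that a false discovery rate correction is applied to the 120-protein panel across proteins, shakes, risk groups and time contrasts, with a separate family for the between-group tests. Name the procedure. Benjamini-Hochberg is a natural choice, but the protocol does not name one even for the genes.
- Select proteins for the incremental area analysis on the adjusted result.
- State that LSD comparisons are made only after a significant F.

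If all nulls are true, Benjamini-Hochberg at 0.05 keeps the chance of any false positive within a family at about 0.05 or less, given independence or positive dependence. Where real effects exist, it limits the expected share of false findings to 5%, not their number.

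The cost is a few sentences and no new data. Fewer proteins will be declared changed, and some modest real changes will be missed.

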# OBJECTIVES

The objectives are formulated to elucidate the effects of the different fatty acids in the high fat loads on gene expression of PBMC in type 2 diabetic subjects compared to healthy obese and healthy lean subjects. The main objective of this study is to elucidate whether the high fat loads (containing either SFA, MUFA or PUFA) will have different effects on PBMC gene expression in the three risk groups of subjects. Secondary objectives are to elucidate the effects of the fat loads in the different risk groups on inflammatory response capacity and endothelial function. Tertiary objectives are to investigate the effect of these fat loads in these subjects on plasma lipid profiles, glucose and insulin and monocyte and lymphocyte gene expression profiles. For more comprehensive phenotyping of the subjects we will also measure body composition, bodyfat distribution and fecal micro flora.

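### For secondary and tertiary outcomes, risk groups are tested shake by shake, which tests neither the general group hypotheses nor group x shake directly, and the pooled ANOVA table has no between-man error to fill the gap

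*Protocol*

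**What the plan says.** The between-group test in section 8 (Statistical analysis) of the protocol reads: "Differences between risk groups for each treatment will be tested by one-way ANOVA followed by LSD correction". It stands in the part of the section that begins "Analysis of secondary and tertiary outcome variables (endothelial function, glucose etc.) will be in SPSS version 15.0". It therefore does not reach PBMC gene expression, which is analysed in LIMMA.

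The design is a cross-over in which "each subject will consume the three shakes and can be used as its own reference". Section 2.1 states the group hypothesis for question 2 as "Obese and type 2 diabetic subjects will have an impaired inflammatory response capacity" and for question 3 as "The high fat load will result in a higher degree of endothelial dysfunction in the high-risk subjects compared to the healthy subjects". Neither names a shake. The neighbouring hypotheses and questions in section 2.1 also expect the fatty acids to act differently, and ask whether the changes differ for high-risk men.

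Section 8 ends with an empty ANOVA table, offered as further detail on the analysis. Its first line is "Risk profile (diabetic, obese, control) | 2" df. Below it come treatment (2), time (2), a single interaction line (8) and error (579). The text does not say whether the per-shake ANOVAs or this table answers the group hypotheses. It states no error control across shakes.

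**The concern.** Section 2.1 raises two kinds of question about the risk groups. One is general: do high-risk men respond worse to a fat load? The other is differential: does the effect of fat type depend on risk group? Three one-way ANOVAs, one per shake, answer neither directly.

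The general question is asked three times, each time on a third of the data each man supplies. LSD after a significant F protects the three group pairs within one shake, but not across shakes. For the differential question, significance under one shake and not under another is no evidence that the shakes differ. The within-group comparisons of shakes elsewhere in section 8 have the same limit, because they are run group by group.

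Two errors in reporting could follow: a chance finding under one of three shakes taken as a group difference, and a difference present under every shake reported as specific to one fat.

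**Working it through.** **The plan's own figure.** 66 men x 3 shakes x 3 times = 594 observations. The table's terms use 2 + 2 + 2 + 8 = 14 df, and 594 - 1 - 14 = 579, as stated. The residual therefore counts all nine values of a man as independent. Risk group varies only between men, so its error has 66 - 3 = 63 df (57 with the 20 per group that section 4.5 expects to complete). Group x shake would have (3 - 1)(3 - 1) = 4 df, so the single 8-df interaction line is not that test.

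**Assumptions.** Two-sided 5% level, 20 men per group. ICC is the share of single-day variance that lies between men. The protocol gives no value, so 0.3 to 0.9 is shown. The effect sizes are illustrative, because the protocol states none for these outcomes.

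**False positives.** Three independent tests would give 1 - 0.95^3 = 14.3%. The same men take all three shakes, so the tests are correlated. Simulation (20,000 runs) gives the first result column below.

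**Pairwise power, equal difference under all shakes.** Relative to one day, the variance of the three-day mean is ICC + (1 - ICC)/3, so the effective d is d divided by the square root of that ratio. Power comes from the noncentral t with 57 df and noncentrality d x sqrt(20/2). On one day this gives 70% at d = 0.8 and 46% at d = 0.6.

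| ICC | At least one false positive in three F tests | Variance ratio | Power on mean, d = 0.8 | Power on mean, d = 0.6 |
|---|---|---|---|---|
| 0.3 | 13.6% | 0.53 | 93% | 72% |
| 0.5 | 12.7% | 0.67 | 86% | 63% |
| 0.7 | 11.2% | 0.80 | 79% | 55% |
| 0.9 | 8.6% | 0.93 | 73% | 49% |

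Example at ICC 0.5: 0.8 / sqrt(0.667) = 0.98, and 0.98 x sqrt(10) = 3.10, which gives 86%.

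**Unequal differences.** At ICC 0.5, a difference of 0.8 under one shake only becomes 0.8/3 = 0.267 on the mean. The effective d is 0.267/0.816 = 0.33 and power is 17%, against 70% for that shake's own test. A difference under two shakes gives 0.533/0.816 = 0.65 and 53%.

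**Conflicting answers.** With groups at 0, 0.4 and 0.8 SD under every shake, the three F tests disagree in about 60%, 51%, 39% and 22% of simulated trials at ICC 0.3, 0.5, 0.7 and 0.9.

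**The pooled line in the table.** Treating the three shake days as independent, with no term for men, gives a type I error of 16%, 23%, 29% and 36% for the risk-group test at the same four ICC values. That is before the three time points are added.

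**The case against.** The strongest reply is that the protocol does ask about shakes. Section 1.2 aims at the effects of the different fatty acids in the risk groups, and the hypotheses beside the two quoted ones predict differences by fat type. The shakes also differ sharply: section 5.1 puts EPA/DHA in one of them only. Group differences under each shake are therefore a legitimate quantity. An average dilutes a difference confined to one shake, as the 17% against 70% shows. This stands. Per-shake comparisons are not off target, and there is no ground for withholding them unless an interaction is significant.

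A reader might also infer that the three-fold replication per man is simply lost. The documents do not support that. The table in the same section pools all three shakes in its risk-profile line. What stands is narrower: that line averages over time, including fasting, and is set against an error without men, so it cannot serve as the group test.

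A reader might further infer that fasting values are compared by shake, which would be meaningless before any shake is drunk. Section 8 does not say so, since it does not define the variable in the per-shake test. Nor does its sentence on incremental areas between risk groups repeat the per-shake restriction. That comparison covers only outcomes already found altered, so it does not replace the main test.

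The order of tests could be left to a statistical analysis plan. But the protocol has itself fixed a test and a table, and they do not agree.

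**Conclusion.** The point holds for secondary and tertiary outcomes. As written, the per-shake ANOVAs test neither the general group difference nor group x shake directly. The only pooled group line lacks a valid error term, and the text does not say which analysis decides.

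The false-positive figure of 8.6% to 13.6% applies where the three tests are read as answers to the one general question. The gain from averaging, from 70% to between 73% and 93% at d = 0.8, rests on an assumed ICC and on an equal group difference under all three shakes. It is small at ICC 0.9, and it becomes a loss when only one shake separates the groups. The documents do not support a claim that averaging is always the more powerful choice. The case for change is that each stated question should have one valid test. The matter is worth correcting, and it does not touch the primary outcome.

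**What to change.** In section 8, analyse each secondary and tertiary outcome in one mixed model of change from T=0, with risk group, shake, group x shake and man as random effect. If the 2-hour and 4-hour changes enter together, add time and a random term for the man's study day. Then state:

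- the group contrast averaged over shakes, on between-man error (about 57 to 63 df), tests the general group hypotheses;
- the group x shake term (4 df) tests whether shake effects differ between groups;
- per-shake group differences, with confidence intervals from the same model, are reported as supporting estimates whatever the interaction shows.

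Correct the ANOVA table to show the between-man error and a separate group x shake line.

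The cost is rewording and a revised table. The data are the same, and section 8 already names a mixed model in the same software. A man with a missing shake day can stay in the analysis. The downside is that the averaged contrast is less sensitive to a difference confined to one shake; the interaction test and the per-shake estimates cover that case.
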